### Study intervention

Patients will be randomized 1:1 using REDcap to either AF ablation with PVI or CSP + AVNA stratified by three prognostic factors: LVEF (≤ or > 40%), QRS width (≤ or > 120 ms), and previous PVI status (first procedure or redo). The study flowchart is shown in *Figure 1*, and the clinical investigation procedures are shown in *Table 3*.

**Figure 1 oeag007-F1:**
[figure not shown]
Study flowchart. Abbreviations: AF, atrial fibrillation; AVN, atrioventricular node; CSP, conduction system pacing; FU, follow-up; LVEF, left ventricular ejection fraction; PVI, pulmonary vein isolation.

**Table 3 oeag007-T3:** Clinical investigation procedures and assessments

	Enrolment	Intervention (within 3 mo)	@ 6 wk^a^ (±2 wk)	@ 6 mo^a^ + each 6 mo (±2 wk)	@ 1 yr^a^ (±2 wk)	End of study visit
Consent form	X					
Randomization	X					
Medical history	X					
Medication	X	X	X	X	X	X
NYHA class	X	X	X	X	X	X
QOL	X				X	
mEHRA score	X	X	X	X	X	X
PROMs					X	
12-lead ECG	X	X	X	X	X	X
Echocardiogram (within 3 months before enrolment)	X				X	
Device check (CSP arm)		X	X	X	X	X
Adverse events		X	X	X	X	X
Mortality status		X	X	X	X	X
End visit form						X

^a^Counted from the date of intervention

Abbreviations: CSP, conduction system pacing; ECG, electrocardiogram; ICF, informed consent form; QOL, quality of life questionnaire (MLWHF + EQ-5D); PROMs, patient-reported outcome measures.

Ablation of AF may be performed according to the operator’s preference (e.g. using radiofrequency ablation, cryoablation, PFA, etc.) and following current European Heart Rhythm (EHRA) recommendations^46^ but should include PVI and restoration of sinus rhythm as goals. Additional lesions (e.g. lines, substrate modification, vein of Marshal ethanol infusion, etc.) may be performed according to the discretion of the operator. Rate and/or rhythm control medical therapy, anticoagulation, and heart failure treatment may be continued after the ablation procedure, as indicated. Operators must have performed >200 AF ablations as a primary operator.

Implantation of CSP (HBP or LBBAP) is currently performed in routine clinical practise^34,35,42,47^ and may be performed according to the operator’s preference and following the technique described in the EHRA consensus document on CSP implantation^47^ but should include conduction system capture (as outlined in the EHRA consensus document of CSP implantation^47^) or left ventricular septal pacing (LVSP) as a goal. With HBP, a backup ventricular pacing lead is preferred, in accordance with the current recommendations.^33,36^ A coronary sinus lead for His-optimized or left-bundle branch optimized CRT (HOT-CRT and LOT-CRT) may be implanted if deemed necessary due to suboptimal paced ECG parameters.^36^ An atrial lead may be implanted at the physician’s discretion if reversion to sinus rhythm is anticipated. If CSP implantation is unsuccessful, the physician may proceed with treatment as clinically indicated, but if possible with BiVP (which is the closest form of physiological pacing), or otherwise with RVP. The generator to be connected to the CSP lead is discretionary. Programming should be optimized to alleviate symptoms, maximize device longevity, and ensure patient safety. Operators must have performed >100 CSP implantations as primary operator.

Radiofrequency catheter AVNA may be performed as a staged procedure or during CSP implantation (also using the superior venous access) according to operator preference (and is not counted as an endpoint).

All procedures should be performed using CE-approved tools and according to instructions for use.

### Sample size calculation and statistical analysis

The event rates extracted from previous studies (see Supplementary material) were evaluated to calculate the required sample size. With a 2 to 3-year recruitment period and all patients being followed up for at least 1 year after randomization of the last patient, the expected mean follow-up duration is 2 years.

For the sample size calculation for the primary superiority hypothesis (mortality + CVH), the expected two-year event rate is 42% in the AF ablation group and 24% in the CSP + AVNA group, which corresponds with a Hazard Ratio of 0.5038. With these event rates, randomization of 2 × 105 evaluable patients provides the trial with 80% power to demonstrate the superiority of CSP and AVNA over AF ablation.

The expected 2-year event rate for the primary noninferiority hypothesis (the composite of all-cause mortality and HFH) is 18% in the AF ablation group and 12% in the CSP and AVNA groups, which corresponds to a Hazard Ratio of 0.6442. With these event rates, randomization of 2 × 105 evaluable patients provides the trial with 80% power to demonstrate the noninferiority of CSP and AVNA compared to AF ablation, with a noninferiority margin of 1.80 for the hazard ratio, which was deemed to be clinically acceptable.

To compensate for loss to follow-up, the study is designed to enrol 220 patients, with follow-up of all patients until at least one year after randomization of the last patient.

The main analysis of the primary endpoints will be conducted in all randomized subjects under application of the intention-to-treat principle at 1-year follow-up of the last enrolled patient (or earlier if recommended by the DSMB based on interim analysis of safety data). The superiority endpoint is declared if the 2-sided *P*-value from the adjusted hazard ratio between groups falls to <0.05. The noninferiority endpoint is declared if the 95%-confidence interval for the adjusted Hazard Ratio from Cox proportional hazards regression model falls below 1.8. The use of 95% confidence interval is equivalent to noninferiority testing with a one-sided type I error (*α*) of 0.025. The hypotheses of the primary endpoints will be tested in a hierarchical order in order to preserve type I error rate of 0.05, i.e. the superiority endpoint will have to be fulfilled for the noninferiority endpoint to be evaluated. There will be no formal interim analyses for early trial termination based on early claims of superiority of CSP and AVNA over PVI ablation.

All statistical analyses of secondary endpoints are descriptive using 95% confidence intervals and no formal hypothesis testing. The 95% confidence intervals are calculated without corrections for multiplicity. Time-to-event secondary endpoints will be analysed using the Kaplan–Meier curves, and hazard ratios will be calculated using Cox proportional hazards regression analysis. Hazard ratios for secondary endpoints that do not include all-cause death will be interpreted as cause-specific hazard ratios, with censoring follow-up at the time of unrelated death. The binary outcomes of the two randomized groups will be compared using logistic regression models. Quantitative secondary endpoints will be described using means and 95% confidence intervals, or medians and interquartile ranges, as appropriate. Changes in quality of life will be analysed with multivariate regression models. An exploratory Win-Ratio analysis^48^ using the components of the primary endpoints will be performed.

The study dataset may be provided to third parties for research purposes only in coded manner where no individual patient identification is possible, and upon agreement between the PIs.

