#### Endpoints

##### Primary endpoints

The study has two co-primary endpoints:

The composite of all-cause death or CVH (superiority hypothesis).The composite of all-cause death of HFH (noninferiority hypothesis).

These endpoints will be evaluated sequentially in a hierarchical order, in order to preserve the type I error rate. The superiority hypothesis has to be fulfilled prior to evaluation of the noninferiority hypothesis (the former is felt to be most relevant and anticipated to be reached more readily and is therefore evaluated first). The main analysis of the primary endpoints is conducted in the full analysis population under application of the intention-to-treat principle, i.e. events are counted regardless of the implementation of the randomized ablation treatment.

The endpoint of CVH includes HFH or admission for any of the following: AF-related symptoms, stroke, acute myocardial infarction, cardiac implantable electronic device (CIED) interventions, redo procedures, or procedure-related complications. Admissions for crossover procedures are counted as CVH endpoints. AVNA during or following CSP implantation is not counted as an endpoint as it is an integral part of the strategy in patients randomized to the CSP + AVNA arm. HFH is defined as admission for worsening HF to a healthcare facility for > 24 h or unplanned hospital visits for HF requiring intravenous diuretics and/or adjustment of other medical HF therapy.

Predefined factors will be evaluated by subgroup analysis (e.g. age, sex, LVEF, heart rate, intrinsic QRS duration, NYHA class, duration of AF, history of AF ablation, etc.).

An independent Clinical Endpoints Committee will adjudicate the primary endpoints and will be blinded to treatment allocation whenever feasible.

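### The 80% power quoted for noninferiority is stand-alone power; under the fixed testing sequence, the power to demonstrate noninferiority is about 70% at the stated 2-year mean follow-up

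*Protocol article*

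**What the plan says.** All references are to the protocol article.

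- **Sample size calculation and statistical analysis, superiority (death or CVH).** The planning assumption is that "the expected two-year event rate is 42% in the AF ablation group and 24% in the CSP + AVNA group". The article converts these rates to a hazard ratio of 0.5038. For 105 evaluable patients in each arm, the stated result is that the design "provides the trial with 80% power to demonstrate the superiority of CSP and AVNA over AF ablation".
- **Same section, noninferiority (death or HFH).** For this composite the planning figure at 2 years "is 18% in the AF ablation group and 12% in the CSP and AVNA groups". The article converts these rates to a hazard ratio of 0.6442. With a hazard ratio margin of 1.80, the same 2 × 105 patients are said to give a design that "provides the trial with 80% power to demonstrate the noninferiority of CSP and AVNA compared to AF ablation".
- **Testing order.** The same section states that "the superiority endpoint will have to be fulfilled for the noninferiority endpoint to be evaluated". The section Primary endpoints says likewise: "The superiority hypothesis has to be fulfilled prior to evaluation of the noninferiority hypothesis".
- **Status.** Noninferiority is one of the two primary goals under Objectives.

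The article gives no power for passing both steps. It does not say that the 80% for noninferiority leaves the sequence out of account.

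**The concern.** Under the fixed sequence, noninferiority is demonstrated only when both tests succeed. The power to demonstrate it is therefore the probability of a joint event. That probability cannot exceed the power of the first test, which the plan sets at 80%. With two 80% tests it would equal 80% only if every trial that passes superiority also passes noninferiority. The endpoints overlap, but not to that degree.

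At stake is the accuracy of a stated design property for a co-primary goal. If every planning assumption is true, the chance of not being able to declare noninferiority on death or HFH is nearer 30% than the 20% a reader would take from the text.

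**Working it through.** **Inputs from the article.** Two-year rates 42% vs 24% (death/CVH) and 18% vs 12% (death/HFH); 105 evaluable per arm; margin 1.80; two-sided 0.05 for superiority and one-sided 0.025 for noninferiority; mean follow-up 2 years; CVH includes HFH, and death is in both composites.

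**Step 1: reproduce the plan's figures.**

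- Hazard ratios: ln(0.76)/ln(0.58) = 0.5038 and ln(0.88)/ln(0.82) = 0.6442. Both match.
- Expected events: 105 × (0.42 + 0.24) = 69.3 and 105 × (0.18 + 0.12) = 31.5.
- Superiority power, Schoenfeld: √(69.3/4) × |ln 0.5038| = 2.854; 2.854 − 1.96 = 0.894, giving 81.4%. With variance 1/44.1 + 1/25.2 it is 78.4%.
- Noninferiority power, Schoenfeld: √(31.5/4) × (ln 1.8 − ln 0.6442) = 2.884; 2.884 − 1.96 = 0.924, giving 82.2%. With variance 1/18.9 + 1/12.6 it is 80.7%. The Freedman form is lower, at 75.6%.

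Both 80% figures are thus reproduced as stand-alone powers.

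**Step 2: joint power by normal approximation.** Take both stand-alone powers as 80% and let the two test statistics have correlation ρ. The joint power is the bivariate normal probability that both succeed.

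| ρ | Joint power |
|---|---|
| 0 | 64.0% |
| 0.3 | 66.6% |
| 0.6 | 69.9% |
| 0.67 = √(31.5/69.3) | 70.9% |
| 0.8 | 72.9% |
| 0.9 | 75.0% |
| 1 | 80.0% |

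With the Schoenfeld values (81.4% and 82.2%) instead, joint power is 66.9% at ρ = 0, 72.4% at 0.6 and 77.1% at 0.9.

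**Step 3: simulation.** Assumptions: exponential event times; death/HFH nested in death/CVH; independent hazards for death/HFH and for other CVH; unadjusted Cox models with Wald tests. Several sets of 5,000 to 8,000 trials were run for 105 per arm over fixed 2 years or 1–3 years; the other rows rest on 4,000 to 8,000 per set. Ranges are across sets.

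| Scenario | Superiority | Noninferiority alone | Both |
|---|---|---|---|
| 105 per arm, fixed 2 years | 80% | 81% | 70–71% |
| 105 per arm, uniform 1–3 years (mean 2) | 79–80% | 81–82% | 70–71% |
| 110 per arm (no loss), 2 years | 82–83% | 83% | 73–74% |
| 105 per arm, uniform 1–4 years (mean 2.5) | 85–86% | 88% | 78–79% |
| 110 per arm, uniform 1–4 years | 87% | 89% | 81% |

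The correlation between the test statistics was 0.57 to 0.60. At 105 per arm and 2 years, about 10% of simulated trials would have met the noninferiority criterion but could not declare it, because superiority had failed.

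**The case against.** The strongest reply is that no printed figure is miscalculated. The section sizes each hypothesis in turn, both 80% figures reproduce, quoting power per hypothesis in a hierarchical design is common, and the sequence is disclosed twice. Joint power might also be given in the full protocol or analysis plan, which is not shown. This stands in part: a reader might infer an arithmetic error, and there is none. It does not rescue the sentence. The sentence attributes the 80%, without qualification, to what the trial can demonstrate, and the trial never runs the noninferiority test on its own.

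Second, 70% is not fixed by the article. It depends on a correlation that is not given, and on follow-up. The article allows 2 to 3 years of recruitment, and its Discussion puts first enrolment in October 2024 and closeout by October 2028. Three years of recruitment plus one gives 1–4 years of follow-up and 78–79%, or about 81% if all 220 patients are also retained. This stands, so it would be too strong to say that joint power cannot reach 80% anywhere in the allowed design range. Those scenarios go beyond the stated 2-year mean, however, and the stand-alone power rises with them (88–89%), so a gap remains. The simulations also use an unadjusted model, while the plan uses adjusted hazard ratios.

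Third, a reader might infer that the reason given for the order, that superiority should be the easier test to meet, is contradicted by equal planned powers. The article does not support that inference. The remark is an expectation, it stands beside a separate argument from relevance, and two powers of 80% fail to support it without refuting it.

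Fourth, one might infer that the trial is too small or the error control flawed. Neither follows. The sequence protects type I error as intended, and superiority keeps its 80%. If superiority fails, nothing stated prevents reporting the death/HFH hazard ratio and its confidence interval; only the formal claim is lost.

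**Conclusion.** The concern holds as a moderate correction to a stated figure. The 80% for noninferiority is stand-alone power. Under the fixed sequence, at the stated rates, 105 evaluable per arm and a 2-year mean follow-up, the power to demonstrate noninferiority is about 70%.

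This assumes exponential times and nested endpoints with independent hazards for death/HFH and other CVH (test correlation about 0.6). With both tests at 80%, the range is about 64% to 75% for correlations from 0 to 0.9. The figure is about 73% if all 220 patients are retained, and about 78–79% with 105 per arm if recruitment takes 3 years and mean follow-up is 2.5 years.

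**What to change.** Keep the sample size, the testing order and the analysis. In Sample size calculation and statistical analysis, label the 80% for noninferiority as stand-alone power and add a sentence such as:

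> Because noninferiority is tested only after superiority has been met, the power to demonstrate it is about 70% with 105 evaluable patients per arm and a mean follow-up of 2 years (assumed correlation between the test statistics about 0.6; about 64% to 75% for correlations of 0 to 0.9), and higher with longer follow-up.

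The sponsor's statistician should replace these values with ones computed under the trial's own assumptions on overlap and accrual. The stated reason for testing superiority first need not be deleted; at most, note that the planning figures give the two tests similar power.

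The cost is wording, and a less favourable stated figure. No patients are added.

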##### Secondary endpoints

Individual components of the primary endpoints and a number of additional endpoints will be evaluated (duration of CVH, reintervention rate, crossovers, CIED implantation or upgrade, sinus rhythm at follow-up, LVEF (evaluated by echocardiography at the study centre), left atrial size, NYHA class, mEHRA score, and quality of life using the Minnesota Living with Heart Failure and EQ-5D-5L questionnaires). Patient-reported outcome measures (PROMs) at 1 year will be assessed by a visual analogue scale questionnaire developed for each study arm based upon PROMs of AF^43^ as well as for living with a pacemaker^44,45^ (see Supplementary material). Healthcare costs and cost-effectiveness will be analysed separately.

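### Kaplan-Meier curves for time-to-event secondary endpoints that exclude death (CVH alone, HFH alone) will overstate cumulative incidence, modestly at 2 years; use Aalen-Johansen estimates instead

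*Protocol article*

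**What the plan says.** The section on sample size calculation and statistical analysis sets one method for all secondary endpoints of this type: "Time-to-event secondary endpoints will be analysed using the Kaplan–Meier curves", with hazard ratios from Cox regression. The next sentence deals with endpoints that do not include all-cause death. Their hazard ratios "will be interpreted as cause-specific hazard ratios, with censoring follow-up at the time of unrelated death".

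The section on secondary endpoints shows which endpoints this reaches: "Individual components of the primary endpoints and a number of additional endpoints will be evaluated". The components of the two composites are death, CVH and HFH, so CVH alone and HFH alone become secondary endpoints without death.

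On the status of these analyses, the plan says: "All statistical analyses of secondary endpoints are descriptive using 95% confidence intervals and no formal hypothesis testing". It names no cumulative incidence function and no other competing-risk method for the curves.

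**The concern.** A patient who dies before being hospitalized can no longer be hospitalized. Censoring at death is legitimate for a cause-specific hazard, because the hazard conditions on being alive and event-free. It is not legitimate for absolute risk. Kaplan-Meier assumes that censored patients would have gone on to have events at the same rate as those still under observation. One minus the curve therefore estimates incidence as if nobody died, and it exceeds the actual incidence whenever anyone dies first.

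The plan thus recognises competing death for the hazard ratio but fixes a curve that ignores it. Because the secondary analyses are estimates with confidence intervals and no tests, the estimates are themselves the result. At stake are the absolute incidence of CVH and HFH in each arm and the absolute difference between arms.

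**Working it through.** **Inputs from the article** (section on sample size calculation and statistical analysis)
- Death or CVH at 2 years: "the expected two-year event rate is 42% in the AF ablation group and 24% in the CSP + AVNA group".
- Death or HFH at 2 years: 18% with AF ablation, 12% with CSP + AVNA.
- 105 evaluable patients per arm; expected mean follow-up 2 years.
- From the Discussion: first enrolment October 2024, closeout expected by October 2028, so at most about 4 years of follow-up.

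**Assumed, because the documents give no death rate**
- 2-year mortality d of 4% or 10%, the same in both arms. Planned mortality cannot exceed the planned death-or-HFH rates of 18% and 12%, and 10% lies below both.
- Constant hazards, with the same death hazard before and after a hospitalization.

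**Plan's own figures.** ln(1 − 0.24)/ln(1 − 0.42) = 0.5038 and ln(1 − 0.12)/ln(1 − 0.18) = 0.6442. Both stated hazard ratios reproduce, so constant hazards match the plan's own conversion.

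**Formulas.** With composite 2-year risk c:
- total hazard h = −ln(1 − c)/2
- death hazard h_d = −ln(1 − d)/2
- event hazard h_e = h − h_d
- one minus Kaplan-Meier: 1 − exp(−h_e·t)
- cumulative incidence with death competing: (h_e/h)·(1 − exp(−h·t))

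**Worked case: CVH, AF ablation, d = 10%, t = 2.** h = −ln(0.58)/2 = 0.2724; h_d = −ln(0.90)/2 = 0.0527; h_e = 0.2197. One minus Kaplan-Meier = 1 − exp(−0.4394) = 35.6%. Cumulative incidence = (0.2197/0.2724) × 0.42 = 33.9%. Excess: 1.7 points.

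**All cases** (one minus Kaplan-Meier vs cumulative incidence, %; excess and shift in points, taken from unrounded values)

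| Endpoint, time | d | AF ablation | Excess | CSP + AVNA | Excess | Shift in between-arm difference |
|---|---|---|---|---|---|---|
| CVH, 2 y | 4% | 39.6 vs 38.9 | 0.73 | 20.8 vs 20.4 | 0.40 | 0.3 |
| CVH, 2 y | 10% | 35.6 vs 33.9 | 1.68 | 15.6 vs 14.8 | 0.77 | 0.9 |
| CVH, 4 y | 4% | 63.5 vs 61.4 | 2.11 | 37.3 vs 36.0 | 1.37 | 0.7 |
| CVH, 4 y | 10% | 58.5 vs 53.5 | 4.94 | 28.7 vs 26.0 | 2.67 | 2.3 |
| HFH, 2 y | 4% | 14.6 vs 14.3 | 0.29 | 8.3 vs 8.2 | 0.17 | 0.1 |
| HFH, 2 y | 10% | 8.9 vs 8.4 | 0.45 | 2.2 vs 2.1 | 0.11 | 0.3 |

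Deaths are equal in both arms here, yet the absolute excess is larger with AF ablation because that arm is planned to have more events. The shift therefore does not need a mortality difference.

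**Scale.** With 105 per arm, the binomial 95% half-width for the 2-year CVH difference is 1.96 × √(0.339 × 0.661/105 + 0.148 × 0.852/105) ≈ 11 points at d = 10%, and about 12 at d = 4%. The shift of 0.3-0.9 points is small beside it. Unlike sampling error, though, it has a known direction and does not shrink with more patients.

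**The case against.** The strongest reply is that the effect is small and nothing decisive depends on it. The co-primary composites include all-cause death, cause-specific hazard ratios are a sound choice for the treatment contrast, and no secondary endpoint is tested. All of that stands, and it limits the point to reporting.

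A second reply is that the censoring wording, "with censoring follow-up at the time of unrelated death", is attached to the hazard ratios, and no sentence says that one minus Kaplan-Meier will be presented as absolute incidence. That is literally correct. But a Kaplan-Meier curve for CVH alone has no other way to handle a prior death, and readers take absolute risks from such curves.

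A third reply is that the article is condensed and the statistical analysis plan is not shown. The full plan may already specify cumulative incidence. The article nevertheless names the method rather than leaving it open, so the point concerns a stated choice.

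Four stronger readings are tempting and lack support:
- **Reintervention, redo and crossover rates are also inflated.** The article lists reintervention and crossovers without calling them time-to-event, and it provides logistic regression for binary outcomes. The point reaches them only if they are analysed as time-to-event.
- **The cost analysis will be distorted.** Costs and cost-effectiveness are to be analysed separately, and nothing says they will use these curves.
- **Death is common, so the bias is large.** No death rate is given, and a life expectancy under 2 years is an exclusion criterion. A 2-year mortality of 15% would exceed the 12% planned for death or HFH with CSP + AVNA. The 4-year figures fall where few patients remain at risk.
- **The bias simply follows the arm with more deaths.** It depends on event frequency as well, and the documents do not say that mortality will differ between arms.

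**Conclusion.** The point holds as a modest reporting flaw with a certain direction. For CVH alone, HFH alone and any other time-to-event secondary endpoint that excludes all-cause death, one minus Kaplan-Meier overstates cumulative incidence.

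Under the assumed 4-10% mortality, the 2-year excess is about 0.7-1.7 points (AF ablation) and 0.4-0.8 points (CSP + AVNA) for CVH, and 0.1-0.5 points for HFH. With equal mortality, the absolute CVH difference moves by about 0.3-0.9 points at 2 years in favour of CSP + AVNA. Late in follow-up the CVH excess can reach about 5 points.

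The size rests on assumed mortality and constant, equal death hazards. If mortality is concentrated after a first hospitalization, fewer patients die first and the excess is smaller. No primary conclusion, error rate or hazard ratio changes.

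**What to change.** For every time-to-event secondary endpoint that excludes all-cause death:
- Replace the Kaplan-Meier curve with the Aalen-Johansen cumulative incidence by arm, with 95% confidence intervals, counting death before the event as a competing event.
- Keep the cause-specific Cox hazard ratio as planned.

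Reserve Kaplan-Meier for endpoints that include all-cause death. If reintervention or crossover is analysed as time-to-event, apply the same rule.

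The cost is a sentence in the analysis plan and a standard procedure. It needs no extra patients or data and has no effect on power. It should be settled before analysis; if the full analysis plan already says this, only the wording needs to be aligned.

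### For LVEF and left atrial size, the plan specifies group description only: no between-arm difference and no use of the baseline echocardiogram or the stratification factors

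*Protocol article*

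**What the plan says.** The protocol article, under Sample size calculation and statistical analysis, sets one frame for all secondary endpoints: "All statistical analyses of secondary endpoints are descriptive using 95% confidence intervals and no formal hypothesis testing". Within that frame it assigns a method to each class:

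- Time-to-event: "hazard ratios will be calculated using Cox proportional hazards regression analysis".
- Binary: "The binary outcomes of the two randomized groups will be compared using logistic regression models".
- Quality of life: "Changes in quality of life will be analysed with multivariate regression models".
- All other quantitative endpoints: "Quantitative secondary endpoints will be described using means and 95% confidence intervals, or medians and interquartile ranges".

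The section Secondary endpoints lists LVEF and left atrial size, and both fall in the last class. Table 3 has a row "Echocardiogram (within 3 months before enrolment", marked at enrolment and again at 1 year. Under Study intervention, randomization is "stratified by three prognostic factors": LVEF cut at 40%, QRS width cut at 120 ms, and previous PVI status.

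**The concern.** The methods for time-to-event and binary endpoints each lead to a contrast between the randomized groups, and quality of life gets a regression model. The sentence for quantitative endpoints leads to group summaries. An interquartile range in particular can only describe a group; it is not an interval for a treatment effect.

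LVEF matters to this comparison. The Introduction reports that the only earlier randomized comparison of PVI with pace-and-ablate favoured PVI on soft endpoints that included LVEF, and that a crossover study found better LVEF with His bundle pacing than with biventricular pacing. Readers will want the LVEF difference between arms with its uncertainty. If they get two separate intervals, some will judge by overlap, which is a much stricter criterion than an interval for the difference. If the contrast is chosen only after the data are in, there are three candidates (1-year value, change from baseline, baseline-adjusted value), and they differ in precision.

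**Working it through.** **Inputs.** The plan gives 105 evaluable patients per arm. It gives no SD and no baseline to 1-year correlation *r* for either echocardiographic outcome, so *r* is assumed over a range and results are in units of the outcome SD. Equal SDs at both times and in both arms are also assumed. The figure of 105 is an upper limit here, since patients who die or miss the 1-year echocardiogram contribute no value; the percentage reductions do not depend on it.

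**The plan's own figure.** The hazard ratio is ln(0.76)/ln(0.58) = 0.5038, as stated. Two proportions of 42% and 24% at 80% power need 106 per arm. With 105 × (0.42 + 0.24) = 69.3 expected events, the Schoenfeld formula gives 81.4% power. The stated 2 × 105 is reproduced, and nothing here challenges it.

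**Precision of a between-arm difference, n = 105 per arm.** The 95% half-width is 1.96 × √(2v/n), where v is:

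- 1-year value alone: v = 1
- change from baseline: v = 2(1 − r)
- linear model adjusted for baseline: v = 1 − r²

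| Assumed r | 1-year value | Change | Baseline-adjusted | Variance cut against 1-year value (r²) |
|---|---|---|---|---|
| 0.3 | 0.271 SD | 0.320 SD | 0.258 SD | 9% |
| 0.5 | 0.271 SD | 0.271 SD | 0.234 SD | 25% |
| 0.7 | 0.271 SD | 0.210 SD | 0.193 SD | 49% |

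The last column is 1 − (1 − r²) = r². The adjusted interval is never wider than the other two.

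**Allowance for stratification on LVEF.** Stratified randomization already balances part of baseline LVEF. Suppose, as an illustration, that the 40% cut lies near the median of a normal distribution and that the strata are balanced. The strata then capture about 2/π = 0.637 of the baseline variance. The true variance of the unadjusted difference is proportional to 1 − 0.637r², and the real saving is 1 − (1 − r²)/(1 − 0.637r²):

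- r = 0.3: 1 − 0.910/0.943 = about 3%
- r = 0.5: 1 − 0.750/0.841 = about 11%
- r = 0.7: 1 − 0.510/0.688 = about 26%

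An unadjusted interval ignores this balance and would be wider than it needs to be. The reported interval therefore still narrows as in the first table.

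**Reading by overlap.** Two separate 95% intervals fail to overlap only when the means differ by 2 × 1.96/√105 = 0.383 SD. A direct interval for the difference excludes zero at 1.96 × √(2/105) = 0.271 SD. Non-overlap corresponds to a two-sided level of about 0.0056.

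**The case against.** This is a journal article that condenses a fuller protocol, and the SAP is not shown. Contrasts and covariates for secondary endpoints are often left there; the article lists no covariates even for its adjusted primary hazard ratios. It also files Cox and logistic contrasts under the heading of descriptive analysis, so that term does not by itself exclude a mean difference. These points stand in part. Per-arm summary is the natural reading of the sentence but not its wording, and the absence of a covariate list would be no finding on its own. What remains is that the article does state a method for this class, and that method is weaker than those stated beside it.

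Several stronger readings are tempting and are not supported:

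- A reader might infer that the trial cannot give an LVEF difference. It can: both echocardiograms are scheduled, and even two arm means with their intervals yield a difference with SE = √(SE₁² + SE₂²). The difference is unspecified, not unobtainable.
- A reader might infer that the plan intends to compare arms by overlapping intervals. It says nothing of the kind; the overlap figures show only what a reader of separate intervals might do.
- A reader might take the r² reduction as the full efficiency gain for LVEF. Stratification at 40% already secures part of it.
- A reader might extend the point to every quantitative endpoint. Quality of life already has a model. PROMs are collected only at 1 year, on a questionnaire developed for each arm, and duration of cardiovascular hospitalization has no baseline value.

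**Conclusion.** The point holds as a minor one. For LVEF and left atrial size, the stated method names neither a between-arm difference nor any use of the baseline measurement or the stratification factors, while the neighbouring endpoint classes get a contrast or a model. The nominal variance reduction available is 9% to 49% for an assumed r of 0.3 to 0.7. For LVEF the real gain is lower, about 3% to 26% under the illustrative assumption about the 40% cut. That baseline left atrial size is available is inferred from the scheduled echocardiogram; Table 3 does not list it separately. No primary analysis, sample size or error rate changes.

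**What to change.** For LVEF and left atrial size, state that the adjusted between-arm mean difference at 1 year will be reported with its 95% CI and without a test. The model is a linear regression of the 1-year value on arm, the baseline value and the three stratification factors (LVEF, QRS width, previous PVI). Apply it to left atrial size where the enrolment echocardiogram measured it. Group means or medians can stay alongside. Leave PROMs and duration of cardiovascular hospitalization as they are on this point. If the SAP already specifies such a model, aligning the article's sentence with it is enough.

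The cost is one sentence of analysis wording, with no new visits or measurements. Fixing it before the data are examined removes the choice among 1-year, change and adjusted comparisons.
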